## Abstract

**Background:**

The prevalence of child and adolescent obesity and severe obesity continues to increase despite decades of policy and research aimed at prevention. Obesity strongly predicts cardiovascular and metabolic disease risk; both begin in childhood. Children who receive intensive behavioral interventions can reduce body mass index (BMI) and reverse disease risk. However, delivering these interventions with fidelity at scale remains a challenge. Clinic-community partnerships offer a promising strategy to provide high-quality clinical care and deliver behavioral treatment in local park and recreation settings. The Hearts & Parks study has three broad objectives: (1) evaluate the effectiveness of the clinic-community model for the treatment of child obesity, (2) define microbiome and metabolomic signatures of obesity and response to lifestyle change, and (3) inform the implementation of similar models in clinical systems.

**Methods:**

Methods are designed for a pragmatic randomized, controlled clinical trial (*n* = 270) to test the effectiveness of an integrated clinic-community child obesity intervention as compared with usual care. We are powered to detect a difference in body mass index (BMI) between groups at 6 months, with follow up to 12 months. Secondary outcomes include changes in biomarkers for cardiovascular disease, psychosocial risk, and quality of life. Through collection of biospecimens (serum and stool), additional exploratory outcomes include microbiome and metabolomics biomarkers of response to lifestyle modification.

**Discussion:**

We present the study design, enrollment strategy, and intervention details for a randomized clinical trial to measure the effectiveness of a clinic-community child obesity treatment intervention. This study will inform a critical area in child obesity and cardiovascular risk research—defining outcomes, implementation feasibility, and identifying potential molecular mechanisms of treatment response.

**Clinical trial registration:**

NCT03339440.

## Background

Cardiovascular disease begins in youth, with obesity as a significant risk factor [1, 2]. Emphasizing the critical need for early prevention and treatment, adult obesity often originates in childhood, and most children with obesity will become adults with obesity. In fact, one in three children in the US are overweight or obese, leading to significant risk for future cardiovascular disease [3]. The American Academy of Pediatrics and the US Preventative Service Task Force (USPSTF) recommend that pediatric providers screen all children aged 6–18 years for obesity annually, using the Centers for Disease Control and Prevention (CDC) sex- and age-specific BMI curves. Additionally, children with BMI at or above the 95th percentile should be referred to a comprehensive behavioral intervention of medium to high intensity, defined as achieving ≥26 h of contact over 6 months [4, 5]. The current recommendation has not met the needs of a diverse population of youth with obesity. Among low-income, racially diverse, and ethnically diverse populations, clinical treatment has not met this recommendation, and has not led to significant reductions in child weight [6, 7].

One central challenge for clinical programs is meeting the recommendation for ≥26 h of contact in a 6-month period. Typical office visits last 15 min; therefore, this requirement amounts to nearly 4 clinic visits every week for the 6-month period. The epidemic currently affects 12.5 million children; current healthcare practices do not have the capacity to absorb this volume of additional visits [8]. Additionally, poor show rates and low family engagement are known barriers to delivering treatment [9]. From the family’s perspective, parents most commonly cite lack of time, cost of travel, and inability to miss work to attend multiple clinical visits, which are sometimes perceived as low-value [10, 11]. The World Health Organization has proposed a new chronic disease model that links healthcare and community settings. In this model, clinic visits serve to screen and treat co-morbid health conditions of obesity, while community centers offer locally-accessible activities during evenings and on weekends engaging the whole family and supporting social interaction.

Prior interventional studies aimed at reducing child obesity have demonstrated a highly heterogenous response to treatment, often leading to no significant BMI reduction [12]. Within these studies there are individuals who are highly responsive to treatment, yet little is known about the factors that predict treatment response. The multi-omic data analysis, including interrogation of metabolite and microbiome features, holds tremendous promise to elucidate the underlying mechanisms and potential variability between individuals and their response to treatment [13]. However, to date, child obesity interventions are focused on clinical outcomes rather than biomarkers that may predict response to treatment. This significantly limits our ability to explain the variability seen in pediatric obesity clinical trials beyond demographics and psychosocial data. Additionally, prior interventional studies have not considered the implementation and dissemination strategy, limiting the replication and ultimate impact of the intervention at the population level. In order to move the field forward, it is critical to leverage interdisciplinary team science and bring together clinical, basic, and population science researchers.

In order to assess the effectiveness of a clinic-community collaboration to treat child obesity we are conducting a randomized controlled trial, called “Hearts and Parks.” This article describes the rationale, objectives, and initial protocol as of April 14, 2020 for the Hearts and Parks trial.

### Rationale for the clinic-community model

#### Clinical obesity treatment

Duke Children’s Healthy Lifestyles program represents the current standard of clinical care for pediatric obesity treatment. Patients meet with multiple providers (medical, nutrition, physical therapy, and mental health) at monthly intervals for 1 year or until the patient’s BMI is in a healthy range. All visits use Motivational Interviewing as a communication strategy [14]. The Healthy Lifestyles clinic is high-volume; 800 new patients aged 2–18 are seen each year, and more than 15,000 children have received care to date. A retrospective case-control cohort study (*n* = 281) demonstrated that patients who complete at least 4 visits in 12 months had a small but significant reduction in zBMI (− 0.03 to − 0.19) [7]. Effectiveness is dose-responsive, and use of text messages leads to a greater number of clinic visits and thus a higher dose. We conducted a prospective, randomized controlled pilot study (*n* = 101) which compared standard care with standard care plus daily text messages, delivered to the parent’s mobile device. Subjects who received texts attended more clinic visits than those not receiving texts (4.3 vs. 1.2, *p* < 0.001) [15].

#### Engagement in community based programs

Bull City Fit is a fitness program delivered through a local Parks and Recreation Department that provides 6 days a week of high-intensity exercise, sports and games, cooking classes, gardening, and swimming. Each session lasts 2 h and is offered to the patient and his or her family members. We have demonstrated that this program is highly engaging among a low-income, racially diverse, and ethnically diverse group. Retrospective baseline data from prior participants of the program (*n* = 500) were supplemented by key informant interviews, focus groups, and surveys to assess participant demographics, attendance, and reasons for participation. Participants believed the program helped them get healthier (96%), attend clinical appointments (85%), and feel more confident exercising in public (72%). The most common reason cited for regular attendance was that peers “look like me” (82%) [16, 17]. High levels of participation in Bull City Fit lead to measureable changes in BMI. A retrospective cohort study (*n* = 271) demonstrated a wide range of attendance, resulting in a range of 10–105 h of participation over 6 months. Higher participation was associated with greater reduction in zBMI (− 0.03 among those participating 20 h or less versus − 0.1 among those participating 80 h or more, *p* = 0.02) [16, 18]. A pilot randomized controlled trial of the clinic-community model demonstrated significantly greater contact hours, as well as improvement in physical activity and quality of life [19].

### Measurement rationale

Although BMI is a central measurement for determining the effectiveness of pediatric obesity interventions, other potential benefits are much broader and deserve equal attention. For this study, we are including a variety of measures to capture these benefits, with particular emphasis on physical fitness, gut microbiome, and peripheral blood metabolites.

#### Physical fitness measures

Physical fitness is often overlooked as a key outcome in child obesity trials, yet fitness confers many cardiovascular health benefits even in the absence of weight loss. Based on the initial work of Blair and colleagues in the late 1980s and early-to-mid 1990s [20, 21], and others following, it is clear that physical fitness is an important predictor of all-cause mortality and disease-free survival for a myriad of conditions; this is true for youth and adults. Recognition of this link is what drove the development of the President’s Council on Physical Fitness in the early 1960’s and the development of physical fitness programs in elementary, middle, and high schools. Furthermore, we know that it is beneficial to be physically fit for a whole host of human medical conditions. Consequently, a favorable outcome of an obesity management program for youth that involves exposure to regular physical activity is the acquisition of a training response manifested as an increase in physical fitness [22].

Vigorous aerobic physical activity, even if intermittent, improves child BMI. An after-school fitness program randomized youth (*n* = 206) with obesity to academic (sedentary) activities or 80 min of moderate-to-vigorous physical activity. Despite only 40% mean attendance, the intervention group demonstrated significant improvements in BMI, body fat percent, and cardiorespiratory fitness [23]. Additionally, child obesity can be reduced with vigorous activity rather than restriction of energy intake [22]. Finally, physical fitness confers both cardiovascular and metabolic health improvements [24].

#### Stool microbiome and metabolic byproducts

The emerging evidence for the intestinal microbiome and its metabolic byproducts as key mediators in the development of obesity and response to treatment is promising. Previously, human observational studies and stool transplantation experiments in animal models (largely focused on adults) using high throughput molecular profiling platforms have found novel interconnections among obesity, insulin resistance, metabolic pathways, inflammation, and intestinal microbiota [25–32]. Recent observational studies in humans and animal models have also established that exercise can influence intestinal microbiota composition with increased efficacy during early life stages, though the consequences on microbiota function are unknown [33]. Studies in adults have also established that dysregulated metabolic pathways can be beneficially modified by exercise [34]. Children with severe obesity mimic adult phenotypes regarding metabolic and cardiovascular risk [35–38]. However, unlike adults, these children are at the earliest stages of disease, have fewer and less severe co-morbid conditions, and tend to be treatment-naïve. For these reasons, children with obesity present a unique opportunity and an ideal population in which to garner deeper insights into the obesity-associated microbiome and related metabolic pathways.

### Objectives

The Hearts & Parks study has three broad objectives: (1) evaluate the effectiveness of the clinic-community model for the treatment of child obesity, (2) define microbiome and metabolomic features associated with child obesity and intervention outcomes, and (3) inform the implementation of similar models in clinical systems.

## Methods/design

The Hearts & Parks trial, https://www.clinicaltrials.gov/ct2/show/NCT03339440, is a randomized controlled effectiveness trial to evaluate *Objective 1*: the integrated clinic-community approach to child obesity treatment compared with routine primary care. The hypothesis is tested through three aims. *Aim 1:* To evaluate the effectiveness of an integrated, clinic-community intervention to reduce child BMI at 6 months as compared with standard of care. We **hypothesize** that (1a) Bull City Fit will lead to a greater 6-month reduction in child BMI than standard care, and (1b) Sustained improvements at 1 year. *Aim 2:* To evaluate the effectiveness of an integrated, clinic-community intervention to improve cardiovascular health at 6 months as compared with standard of care. We hypothesize that Bull City Fit will lead to a greater 6-month improvement in (2a) peak heart rate during a cardiorespiratory fitness challenge and (2b) blood pressure and blood lipids, as compared with standard care. Finally, we include several secondary and exploratory outcomes, focused on social and emotional health, parent outcomes, and sleep.

Utilizing the subjects enrolled in the Hearts & Parks trial, we address *Objective 2*: examining microbiome and metabolic pathways. These aims include (1) identify associations that will inform the discovery of novel microbiota-related molecular pathways associated with obesity and cardiovascular fitness; (2) identify biomarkers that predict successful BMI reduction and exercise intervention efficacy in children and adolescents with obesity; (3) determine whether microbiome related molecular pathways are modifiable through programs of BMI reduction and exercise; and (4) determine how these pathways and biomarkers change as a function of life stage and disease status across the lifespan.

To address *Objective 3*, informing the implementation of the intervention in clinical and community systems, we use the Reach, Effectiveness, Adoption, Implementation and Maintenance (RE-AIM) [39] framework to measure and report facilitators and barriers to patient engagement, retention, successful outcomes, and project sustainability.

### Study design

The objectives above will be achieved through the completion of a prospective, randomized clinical trial as described in detail below. The study flow diagram (Fig. 1) highlights the recruitment, enrollment, randomization, and assessments for the study. We will use a two-arm, randomized crossover controlled trial to compare routine primary care management of childhood obesity versus a novel clinic-community partnership program to treat childhood obesity. This design will allow for a randomized comparison of Group 1 (6-month standard control) to Group 2 (immediate 6-month intervention program) and to Group 3 (delayed crossover intervention on the standard control group). The design will also allow us to observe intervention effects at 3 months in both intervention groups (Groups 2 and 3), and to track Group 2 for 6 additional months after active intervention to assess whether health benefits seen at 6 months were sustained to 12 months.

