#### Randomization

Patients who consent for participation will undergo randomization in a 1:1 ratio following the baseline visit. Randomization occurs using the Research Electronic Data Capture (REDCap) system. Research coordinators notify patients of their assigned group following the baseline visit. Given the nature of the intervention, it is not possible to blind patients or providers to treatment assignment; therefore, unblinded randomization will be conducted.

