### Intervention

Subjects randomized to the intervention group enroll in the clinic-community intervention for 6 months. This includes Healthy Lifestyles clinic visits at baseline, 3-months, and 6-months, and twice-weekly sessions at the community center as described above. The clinic visits will include 30-min medical, dietary, and physical activity evaluation and counseling sessions. The sessions at the community center involve 30 min of warm up/check in time, at least 60 min of moderate-to-vigorous physical activity and 30 min of nutrition education. In total, subjects who participate fully will receive 4.5 h of clinical counseling, 52 h of physical activity, and 26 h of group-based nutrition counseling (108.5 h). In order to meet the recommended ≥26 h of contact over a 6-month period, subjects will need to participate in at least 25% of offered activities [5]. To enhance engagement and reinforce teaching, thrice-weekly text messages are sent to parent and child (if aged 11 or older, with parental permission) for the 6 months of the intervention. Within the community center, posters display playful characters designed to educate families about the experience and purpose of particular bodily sensations (e.g., Harold the Hunger Pain, Betty the Butterfly). These characters are further reinforced via text messages in which characters are reiterated, further information about that bodily sensation is provided, and information provided to increase interest in a variety of foods. Finally, monthly cartoon videos are designed to provide entertaining and accessible ways to put complex constructs like emotional eating and parent responsiveness into action.

The comparison group is an enhanced, 6-month wait list group. During the wait time, subjects will receive a non-obesity-related literacy intervention. This control intervention is consistent with Good Clinical Practice for the target population, as low-income families have fewer age-appropriate books per child in the home, and educational success is strongly mediated by literary skills [41, 42]. We will provide a $15 gift card each month to a locally owned book store in Durham. At the end of the 6-month wait time, subjects will be invited to participate in the intervention group.

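### Group 1 versus Group 3 is called a randomised comparison, but Group 3 is the control arm itself after month 6

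*Protocol article*

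**What the plan says.** All references are to the protocol article.

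- **Design label** (Study design): "We will use a two-arm, randomized crossover controlled trial to compare routine primary care management of childhood obesity".
- **Contrasts claimed** (Study design): "This design will allow for a randomized comparison of Group 1 (6-month standard control) to Group 2 (immediate 6-month intervention program) and to Group 3". The same sentence defines Group 3 as "delayed crossover intervention on the standard control group".
- **Allocation** (Randomization): "Patients who consent for participation will undergo randomization in a 1:1 ratio following the baseline visit". No second randomisation is described.
- **Route into Group 3** (Intervention; Data collection strategy): controls are invited into the intervention when the wait ends. Their 6-, 9- and 12-month visits then serve as intervention baseline, month 3 and month 6.
- **One-year follow-up** (Study design): the plan will "track Group 2 for 6 additional months after active intervention to assess whether health benefits seen at 6 months were sustained to 12 months". Under Methods/design, hypothesis 1b expects the improvement to last to 1 year.
- **Named intervention and comparator**: hypothesis 1a reads "Bull City Fit will lead to a greater 6-month reduction in child BMI than standard care", and the Aim 2 hypothesis also names Bull City Fit. The aims themselves name the integrated clinic-community intervention. The Intervention section gives that arm Healthy Lifestyles visits, community sessions, texts and videos. On the control side: "The comparison group is an enhanced, 6-month wait list group", with a literacy programme. The rationale says "Healthy Lifestyles program represents the current standard of clinical care for pediatric obesity treatment", while Study design makes routine primary care the comparator.

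**The concern.** The article gives a contrast a property that the allocation cannot supply. A reader, or a later analyst relying on this text, could report the change in controls after they start the intervention, set against their own earlier change, as if chance had decided who was in each group. Nothing in the design protects that contrast from the passage of time, ageing, regression to the mean after entry at or above the 95th percentile, or the loss of some children and the non-uptake of others.

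The *crossover* label reinforces the misreading. In a crossover trial the reverse sequence separates treatment from period, and here that sequence does not exist.

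Two related statements need the same care. By month 12 every control has been offered the intervention, so sustained benefit has no untreated comparator. And two hypothesis statements name one component against standard care, although the trial compares a package with a wait list.

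**Working it through.** The point is one of design, so the check is to set the statements side by side and ask what each contrast estimates.

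1. **Groups and allocation.** There are two arms and one 1:1 randomisation after baseline. Group 2 is one arm. Groups 1 and 3 are the other arm before and after month 6.

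2. **What Group 2 versus Group 1 estimates.** Let Y0, Y6 and Y12 be a child's outcome at months 0, 6 and 12. Let d1 and d2 be the mean changes that would occur without intervention in months 0–6 and 6–12, and let t be the intervention effect.
 - Group 2, mean of (Y6 − Y0) = d1 + t
 - Group 1, mean of (Y6 − Y0) = d1
 - Difference = t

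 The drift d1 cancels because both arms pass through the same interval and were formed by chance. Loss to follow-up still matters here, as in any trial, but the contrast is randomised.

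3. **What Group 3 versus Group 1 estimates.** Assume the same effect t in the second interval, and no carry-over from the wait-list period.
 - Group 3, mean of (Y12 − Y6) = d2 + t
 - Group 1, mean of (Y6 − Y0) = d1
 - Difference = t + (d2 − d1), plus a selection term if those who start and finish Group 3 differ from those measured in Group 1.

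 Nothing in the design makes d2 equal to d1, and no reverse sequence exists from which to estimate d2 − d1. Within one child the contrast is (Y12 − Y6) − (Y6 − Y0) = Y12 − 2·Y6 + Y0. The month-6 value is both the end of the control period and the start of the intervention period, so an error in it counts twice.

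4. **How many children it concerns.** The Sample size section gives 270 children and 30% lost before 6 months. At 1:1, 270/2 = 135 controls. If the loss is equal in both arms, 135 × 0.70 = 94.5, so about 94 controls remain to be invited. The article gives no uptake rate, so Group 3 could be smaller.

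5. **What the 9- and 12-month visits allow.** Data collection strategy measures both arms at 9 and 12 months. Comparing the arms as allocated at those visits is still randomised. It estimates the effect of immediate versus delayed start, not of intervention versus control. Following Group 2 alone from 6 to 12 months is a within-group description.

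6. **What the primary contrast compares.** The intervention arm receives clinic care, community sessions, texts and videos. The control arm waits, with book gift cards. No arm isolates Bull City Fit, and no arm receives Healthy Lifestyles alone.

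**The case against.** The strongest reply is that no stated analysis uses the Group 1 versus Group 3 contrast. General analytic approach targets the 6-month change between intervention groups by intention to treat, and Sample size is based on 6-month zBMI. That stands: the primary result is not put at risk by the faulty sentence. It does not rescue the sentence, which asserts a property the design lacks.

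It can also be said that the one-way delayed start is described plainly elsewhere, so *crossover* is only a label; that Study design presents the 12-month follow-up openly as tracking Group 2 and does not call it randomised; and that Bull City Fit is shorthand confined to the hypothesis sentences. These replies are fair. They limit those items to clarification and alignment.

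Several stronger readings are tempting, and the documents do not support them:

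- *The before-after contrast inflates the benefit by a known amount.* A reader might take the zBMI change of −0.03 at 20 hours or less (Engagement in community based programs) as background drift, and call it 30% of the 0.10 target (0.03/0.10). Those children attended the programme, so the figure is not untreated drift. The direction is open too: regression to the mean after selection at entry would fall mainly in months 0–6 and could make Group 3 look worse. zBMI, being standardised for age and sex, removes part of the growth effect.
- *Clinic care alone could account for the whole target.* The range −0.03 to −0.19 under Clinical obesity treatment applies to patients who completed at least 4 visits in 12 months. The trial schedules three clinic visits in the 6-month intervention.
- *Everything after month 6 is uncontrolled.* Both arms are measured at 9 and 12 months, so immediate versus delayed start remains a randomised comparison.

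**Conclusion.** The point holds in a limited form. Calling Group 1 versus Group 3 randomised is wrong on the article's own account of its groups, allocation and visit schedule. The contrast is a before-after comparison within the control arm, with bias of unknown size and direction. The design is a delayed-start wait-list trial. The only randomised comparison of intervention with control is Group 2 versus Group 1 over months 0–6, and that comparison is unaffected.

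The 12-month tracking of Group 2 has no untreated comparator, but the article does not claim a randomised one, so a label is enough. The naming of Bull City Fit is a mismatch between hypotheses and aims, not evidence that results will be credited to the wrong component.

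The conclusion assumes that Group 3 consists only of children first allocated to control, as Study design and Data collection strategy both say. The study diagram was not available to check.

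**What to change.** Edit the Study design, Methods/design and General analytic approach text:

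1. Remove *randomized* for Group 3, and call its comparison with Group 1 a within-child, non-randomised analysis.
2. Replace *crossover* by *wait-list (delayed-start)*.
3. State that the only randomised intervention-versus-control contrast is Group 2 versus Group 1 over months 0–6, and that the primary effect is estimated from those visits.
4. Label hypothesis 1b as within-group maintenance without an untreated comparator. Describe any 9- or 12-month comparison of the arms as immediate versus delayed start: randomised, but answering a different question.
5. Reword hypotheses 1a and 2 to match the aims: the integrated clinic-community intervention versus the enhanced 6-month wait list with routine primary care.

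The cost is wording. No extra children, visits or data are needed. The price is a more modest claim for Group 3 and for the 1-year result.
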